### Sample size

Based on the results of the pilot study and related studies, the number of alters motivated by the index through standard secondary distribution was set at 0.65, and through the secondary distribution with monetary incentives, was set at 1.0, assuming equal variance between the two groups, we used a standard deviation of 0.5 for all groups [16, 27]. We set the required sample size at 100 people, for a total of 200 people, with an alpha of 0.05, a power of 0.90, and a lost follow-up rate of 0.20.

### Data management

All data will be stored electronically at JINSHUJU, a secure online platform that records HIVST kit application information, questionnaire information, and uploaded test results. A contractual agreement with JINSHUJU and JINSHUJU’s encryption system guarantee the privacy of the data. Only project researchers have access to the JINSHUJU, thus ensuring the security and privacy of participants. When transferring data, some identifiable variables (such as phone numbers and addresses) will be encrypted to protect privacy. During the trial, participants will be contacted on a daily basis using a specific phone for telephone support and post-test consultation.

### Missing data plan

Index participants will be involved in the baseline survey and the subsequent three-month follow-up survey, and alter participants will be involved in the online questionnaire phase when tests results are uploaded. However, for our primary and secondary outcomes, data may be missing. For participants missing at follow-up, we will document the reason for missing data and use suitable imputation to improve the robustness of the study results.

### Data analysis

All statistical analyses will follow the intention-to-treat principle. We will use descriptive analysis to report baseline characteristics. For baseline differences between index participants who completed the 3-month follow-up survey and those who did not, we will use a two-sample t-test for comparison if the data are normally distributed and a chi-square test if not. A p-value less than 0.05 is considered statistically significant.

Considering the distribution of the results and based on related studies, we will use zero-inflated negative binomial regression for the primary outcome analysis [27, 28]. The primary outcome analysis will compare the differences between the control and intervention groups. Then the incidence rate ratio (IRR) and its associated 95% CI will be estimated further to compare the primary outcome difference between the two groups. For the secondary outcome analysis, we will compare differences in the mean number of alters who tested positive for HIV recruited by index participants in each group and further assessed by IRR and its associated 95% CI. In addition, we will also apply logistic regression for the secondary outcome analysis. We will perform a subgroup analysis of the first primary outcome, stratified by statistically significant factors. All IRRs will be adjusted by index participant-related factors.

If possible, we will conduct an economic evaluation by using micro-costs to assess the total cost per group, the cost per person tested and the cost per HIV diagnosed for each group. Also, we will compare the cost-effectiveness in the two groups, intervention and control groups.

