### Study measures

For the baseline survey, index participants who meet the inclusion criteria will complete the baseline questionnaire. We will collect socio-demographic characteristics (age, gender, marital status, the highest level of education completed, and monthly income), sexual behavior (previous sex, role during sex with men, condom use, number of sexual partners, and drug use), influence within personal social circles, previous HIV testing experience and their social network.

After three months, we will follow up with the index MLWH, asking them about the distribution process, focusing on their experience and attitude in distributing the self-test kits and their willingness to recommend them. In addition, when alters upload their results, they will also be required to complete a questionnaire online. We will ask about their socio-demographic characteristics, sexual behavior, the experience of previous HIV testing, experiences and attitudes toward using HIVST kits, and their social network.

Participants are required to collect their fingertip blood samples according to the instructions for use. All blood samples will be analyzed using the SD Bioline HIV/Syphilis duo test kits (SD Bioline, Company, South Korea). The trained staff at CBO will examine the resulting photographs and provide corresponding post-test consultation, which will be recorded in the JINSHUJU.

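### The attrition check switches from a t-test to chi-square when data are not normal; for skewed numeric baseline variables such as age this costs sensitivity

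*Protocol article*

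**What the plan says.** The Data analysis section of the protocol article sets one rule for the attrition comparison. It opens "For baseline differences between index participants who completed the 3-month follow-up survey and those who did not" and continues "we will use a two-sample t-test for comparison if the data are normally distributed and a chi-square test if not". The threshold follows: "A p-value less than 0.05 is considered statistically significant". No rank-based test is named anywhere in the article, and no grouping of numeric variables is described.

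The variables to be compared are those of the baseline questionnaire, listed under Study measures. They are of mixed type. One group is "socio-demographic characteristics (age, gender, marital status, the highest level of education completed, and monthly income"; the sexual-behaviour items include "number of sexual partners" beside categorical items such as condom use.

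The Sample size section gives the expected scale of loss: "for a total of 200 people, with an alpha of 0.05, a power of 0.90, and a lost follow-up rate of 0.20".

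**The concern.** Whether a t-test or a chi-square test applies depends first on whether the variable is numeric or categorical. The stated rule asks only whether it is normal. For categorical items it arrives at the right test by accident, since they are not normal and so go to chi-square. For a numeric item that is not normal it arrives at the wrong one. The usual alternative there is a rank test, which keeps the ordering of the values.

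An analyst who follows the sentence for a skewed numeric variable has two choices. One is to cut it into categories that nobody has specified. The other is to tabulate every distinct value, which gives a sparse table. Both ignore order.

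What is at stake is the reading of attrition. The Discussion names loss to follow-up as a possible source of bias, and the Missing data plan foresees imputation. A non-significant result from an insensitive test could be taken as evidence that loss was not selective.

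**Working it through.** The article states no figure for this comparison, so there is nothing of its own to reproduce. The check is of how the rule behaves at the planned size.

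**Inputs from the article.** Total 200 and loss 0.20 (Sample size); significance level 0.05 (Data analysis; taken here as two-sided).

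**Group sizes.** Lost: 0.20 × 200 = 40. Retained: 200 − 40 = 160.

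**Sparseness.** If a value is held by m of the 200 people, its expected count in the lost group is m × 40/200 = 0.2m. This is below 5 whenever m is below 25. Age in years has many values, and few would be shared by 25 people.

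**Limiting case.** If every value is distinct, the table is 2 × 200 with all column totals equal to 1. Pearson's statistic is N × (Σ O²/(row total × column total) − 1) = 200 × (160/160 + 40/40 − 1) = 200, on 199 degrees of freedom. It takes this value whoever is lost, so the test can never reject.

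**Simulation.** 160 against 40, 2,000 runs per case, two-sided 0.05. The distributions are assumptions, because the article gives none:
- Continuous: lognormal, log-mean 8.5 (retained) and 9.0 (lost), log-SD 0.8.
- Age in whole years: 18 plus a gamma variable of shape 2, scale 7 (retained) and 10 (lost), rounded down. The means before rounding are 18 + 2 × 7 = 32 and 18 + 2 × 10 = 38.
- Skewed count: negative binomial with size 0.6, mean 3 (retained) and 6 (lost).

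Under the null, both groups follow the retained distribution.

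| Variable | Expected counts below 5 | Chi-square, raw values: null / shift | Chi-square, median split: null / shift | Rank-sum: null / shift |
|---|---|---|---|---|
| Continuous | 100% | 0% / 0% | 4.4% / 81% | 4.2% / 93% |
| Age in years | 83–85% | 4.4% / 45% | 5.0% / 57% | 5.4% / 75% |
| Count | 74–77% | 4.1% / 63% | 4.9% / 42% | 4.7% / 60% |

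The simulation standard error is about √(0.05 × 0.95/2000) = 0.5 percentage points near 5% and √(0.6 × 0.4/2000) = 1.1 points near 60%.

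A separate simulation at the same group sizes, with its own assumed distributions, showed the same pattern. Chi-square on raw values against rank-sum gave 0% against 91% (continuous), 43% against 91% (age in years) and 66% against 70% (count, with type I error 4.6%). A median split gave 77% and 70% against 91% for the continuous variable and age.

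**Reading.** Chi-square loses sensitivity on age and on a continuous variable, whether raw or split at the median. For a count tabulated by value, the error rate holds and the power is close to that of the rank-sum test. There the remaining objections are sparse cells, ignored order, and a test of any difference in distribution rather than of location. The count loses clearly only if it is split (42% against 60%).

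**The case against.** The strongest reply is that this is loose wording in a descriptive check. The authors probably meant chi-square for categorical items, and a trained analyst would not tabulate 200 distinct values. The 0% result is indeed a limiting case that the article does not say it will produce. The wording still stands as the stated rule, though, and nothing else in the article corrects it. A median split, the milder way of following it, also loses power.

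Four further points on the other side hold.
- A reader might infer that chi-square is invalid for the partner count because most expected counts fall below 5. The simulations do not support that: type I error was 4.1% and 4.6%, with little or no loss of power.
- The article does not say whether income or partner number is recorded as a number or in bands. If banded, chi-square is usable, though it ignores the order of the bands. Network size is not a listed variable; Study measures refers only to the social network and to influence within it.
- This is not the only safeguard. The Missing data plan records reasons for missingness and imputes, and the Discussion adds a consistency check of questionnaire variables before and after follow-up. Neither compares lost with retained indexes at baseline.
- A reader might infer that the primary result is at risk. The primary model is a zero-inflated negative binomial regression that does not use this test. Under the control-group description, a distribution counts as successful when an alter returns a result, linked to the index by the number on the return card. An index who skips the three-month survey can therefore still have his alters counted.

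**Conclusion.** The concern holds as a wrong stated rule of minor weight. Chi-square is not what replaces the t-test when a numeric variable is skewed, and age is a listed variable that can trigger the rule. At about 40 lost against 160 retained, following it cost roughly 18 to 30 percentage points of power for age in the tabulated simulation (57% or 45% against 75%) and at least 12 points for a continuous variable (81% against 93%). For a count tabulated by value there was no material cost.

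These sizes rest on the assumed distributions and shifts, and on loss running at 20%. The pattern is firmer than the individual figures. Because this is the only baseline comparison of lost and retained indexes that the article states, selective loss could be missed. The documents do not show that the primary estimate would change.

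**What to change.** Replace the sentence with a rule by variable type:
- categorical variables: chi-square test, or Fisher's exact test where the table is sparse;
- approximately normal numeric variables: two-sample t-test;
- other numeric or count variables: Wilcoxon rank-sum test.

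Showing the comparison by arm is optional. It would be informative because only one arm is paid for returned results, but it does not follow from the error itself.

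The change is one sentence and needs no new data. The Trial status section says that statistical analysis has not begun, so it can be made before any result is seen.

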### Outcomes

Our primary outcome will be (1) the mean number of alters motivated by each index in each group, which will be compared between the two groups; (2) the mean number of newly tested alters motivated by each index in each group. Secondary outcomes will be (1) the mean number of alters who tested positive for HIV recruited by index participants in each group; (2) the cost per person tested and HIV diagnosed for each group.

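### Subgroups for the first primary outcome are to be chosen by an undefined significance rule, so the choice depends on the trial's own results, and no test of a differing incentive effect is stated

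*Protocol article*

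**What the plan says.** The subgroup plan is one sentence in the Data analysis section of the protocol article: "We will perform a subgroup analysis of the first primary outcome, stratified by statistically significant factors". The outcome concerned is defined under Outcomes as "the mean number of alters motivated by each index in each group, which will be compared between the two groups".

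The only threshold in the Data analysis section is "A p-value less than 0.05 is considered statistically significant". It follows directly on a comparison of indexes who did and did not complete the 3-month survey. For the main analysis, "we will use zero-inflated negative binomial regression for the primary outcome analysis", and "All IRRs will be adjusted by index participant-related factors". Neither sentence names a factor or an arm-by-factor term.

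Study measures lists the baseline items that could be screened:
- socio-demographic: "age, gender, marital status, the highest level of education completed, and monthly income"
- sexual behaviour: "previous sex, role during sex with men, condom use, number of sexual partners, and drug use"
- other: "influence within personal social circles, previous HIV testing experience and their social network"

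No other section mentions subgroups, interaction or effect modification.

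**The concern.** A subgroup analysis asks whether the incentive works better for some index participants than for others. The article instead fixes a rule that chooses the factors by significance and leaves open what they are significant for. That raises three problems.

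- The list of subgroups is not known until the data have been examined, so readers cannot tell how many factors were tried.
- If significance means association with the number of alters, the rule answers a different question. A factor can predict how many kits are distributed without changing the effect of the incentive. A factor that does change the effect may have no average association with the outcome, and would then be passed over.
- With no interaction test stated, the natural reading of the output is to set one stratum's IRR and p-value against the other's. That comparison does not test for a difference.

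At stake is the credibility of the subgroup results for the first primary outcome, not the main comparison.

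**Working it through.** The article gives no number for the subgroup analysis, so there is none to reproduce. The check borrows inputs from the Sample size section: means of 0.65 and 1.0 (difference 0.35), SD 0.5 in both groups, 100 per group and 20% loss, which leaves 80 evaluable per arm. (Those inputs give 43 per arm for 90% power two-sided, or 54 after allowing for loss, rather than 100. That is a separate matter and does not affect this point.)

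**1. What the rule could mean**

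| Significant for | What is selected | Depends on trial data? |
|---|---|---|
| number of alters | prognostic factors | yes |
| difference between arms at baseline | chance imbalance under randomisation | yes |
| difference between completers and non-completers | factors linked to attrition | yes |
| interaction with arm | apparent modifiers, with only the significant ones shown | yes |

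**2. Chance selection.** Study measures lists 5 + 5 + 3 = 13 items. With k independent factors, none related to whatever is tested, P(at least one passes) = 1 − 0.95^k:
- k = 5: 1 − 0.774 = 22.6%
- k = 10: 1 − 0.599 = 40.1%
- k = 13: 1 − 0.513 = 48.7%

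Thirteen is generous. Under the Eligibility criteria every index was assigned male at birth, has had anal sex with men and is living with HIV. Gender, previous sex and previous HIV testing may therefore vary little, and 13 − 3 = 10. Correlated items lower the figure further.

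**3. Prognosis is not modification.** Assume a binary factor that splits each arm in half (40 per arm per stratum), a normal outcome with SD 0.5, and two-sided 0.05.
- SE of the factor's average association = 0.5 × √(2/80) = 0.0791.
- SE of the arm-by-factor difference = 0.5 × √(4/40) = 0.158.
- Purely prognostic factor (assumed difference 0.25, no interaction): 0.25/0.0791 = 3.16, so the chance of selection is Φ(3.16 − 1.96) ≈ 88%. Its interaction test is significant in 5% of trials.
- True modifier (assumed interaction 0.35, no average association): selected in 5%, although its interaction test is significant in Φ(0.35/0.158 − 1.96) ≈ 60%.

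A simulation of 20,000 runs gave 88% and 5% for the first factor, and 5% and 60% for the second.

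**4. Comparing stratum p-values.** Let the effect be 0.35 in both strata.
- SE within a stratum = 0.5 × √(2/40) = 0.112, and 0.35/0.112 = 3.13.
- Power in each stratum = Φ(3.13 − 1.96) ≈ 0.879.
- P(one significant, the other not) = 2 × 0.879 × 0.121 ≈ 21%. The simulation also gave 21%.

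**5. What a proper test could detect.** With the same split, power for an interaction of 0.35, as large as the whole planned effect, is about 60% with 80 per arm and 70% with 100. For 0.175 it is about 20% and 23%. Reaching 90% for 0.35 needs 4 × 2 × (0.5 × 3.24/0.35)² ≈ 172 evaluable per arm.

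**Limits of steps 3 to 5.** They use mean differences and assumed effect sizes, not the zero-inflated count model, and on the ratio scale the prognostic example would differ. The 21% in step 4 also holds for a factor with no link to the outcome at all, for which there is no interaction on either scale.

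**The case against.** The strongest reply is that the article never says what the factors must be significant for. If it means a significant interaction with arm, a test of differing effect is implied. The full analysis plan, which is not shown, could also hold an interaction test. Both points stand. The supportable statement is that no such test is stated here, not that none is planned, and the prognostic reading is one of several. The reply does not rescue the rule, because showing only the factors with a significant interaction is still selection on results. A further reading, that the factors come from the related trial cited for the primary model, would not depend on this trial's data, but nothing in the text supports it.

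A second reply is that 49% overstates the matter. This stands in part. The figure assumes independence and counts nearly constant items, which is why a range is given. It is also the chance that an unrelated factor becomes a stratifier, not the chance of a false subgroup claim. The harm from reading stratum p-values against each other is the separate 21%.

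A third reply is that small strata are no argument against the rule. That is correct: a pre-named factor split at its median leaves the same 40 or so per arm, and three clinics average about 80/3 ≈ 27. Small strata are a reason to label the results exploratory, whichever way the factors are chosen.

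**Conclusion.** The point holds as a defect in a stated rule, not as a missing detail. The article fixes how subgroups are chosen, leaves the criterion undefined and, on every reading tied to its own data, lets the results choose them. The size is a 23% to 49% chance of selecting at least one unrelated factor among 5 to 13 (independent tests at 0.05), and about 21% discordant stratum p-values with no true difference (normal outcome, equal strata, 80 evaluable per arm).

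A reader might go further and infer that the trial will make false subgroup claims about half the time, that it will never test for interaction, or that its subgroup results will decide who is offered incentives in later programmes. The documents support none of these. The percentage concerns selection only, the full analysis plan is not shown, and no section ties subgroup results to a roll-out decision. The Objectives and Hypotheses concern the overall effect. The primary comparison between arms is unaffected, so this is a worthwhile correction to a supportive analysis and not a threat to the trial's main conclusion.

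**What to change.** Replace the sentence with a short list of baseline factors named before the analysis starts; the Trial status section says it had not begun at the time of writing. The data are already collected. Candidates are clinic (three sites), number of sexual partners, and the index's influence among social contacts. These are examples only: the article gives no evidence that they modify the effect, and the final choice belongs to the investigators. For each factor:

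- add an arm-by-factor term to the primary count model and report the ratio of IRRs with its 95% CI;
- show the IRR and 95% CI in every stratum, whatever the p-value;
- label the results exploratory and say that power is low (about 60% even for an interaction as large as the planned effect, under the assumptions above).

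The cost is wording only. The downside is that any subgroup outside the list becomes post hoc and must be reported as such. The fix makes the reporting honest; it does not make the trial large enough to find moderate effect modification.

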## Discussion

Enhancing HIV testing services among MSM is essential for HIV control [29, 30]. Secondary distribution of HIVST based on social networks of MSM is feasible and contributes to the uptake of HIV testing in Chinese MSM [16, 27]. However, few studies have evaluated interventions directly imposed on the social networks of PLWH to increase awareness and prevention of HIV. This study will extend the existing literature by implementing secondary distribution of HIVST among MLWH only, promoting partner testing and friends testing, and assessing whether monetary incentives can improve its effectiveness.

Several limitations should be considered in this study. First, even if the self-test kits are free, the deposit set for each kit may discourage order and distribution by participants who may have to cover the deposit expenses for their peers. This study has minimized the deposit threshold to a deposit amount of 0.01 RMB per kit, which is affordable for everyone to ensure that the deposit does not become a barrier for participants to apply for self-test kits. Second, due to the three-month interval between follow-up surveys, follow-up data may be lost during the information collection process resulting in biased results. As compensation, the researchers will evaluate whether some of the participants’ questionnaire variables are consistent before and after follow-up. Third, participants may migrate if the study period is long. To avoid this situation, we will closely track participants and remind them to contact us promptly to update their phone numbers or WeChat. Finally, from an implementation and outreach perspective, although each participant can apply for HIVST kits multiple times, there is only a maximum of five requests per person, which may not meet the needs of participants willing to distribute as many self-test kits as possible. However, we can address this issue by removing the limit in the future implementation study.

New strategies for more targeted and effective testing are needed to sustain HIV services during the COVID-19 pandemic. HIVST does not require direct contact interaction, which can meet the unique planning needs and global HIV testing goals during this period and over the long term [31]. In addition, the secondary distribution of social network-based allows marginalized populations to receive free HIV self-testing at a very low threshold, which their friends turn in. It will reach marginalized, high-risk MSM hidden in current HIV testing practices and encourage intra-network conversations about risk behaviors, HIV testing, and HIV status, further promoting accurate HIV intervention and control. A randomized controlled trial showed that monetary incentives effectively promoted the secondary distribution of HIVST and expanded HIV testing among MSM [27]. Building on this, our study will further narrow the target population to focus on PLWH, thus further validating whether it can more efficiently identify new HIV-positive cases and facilitate ART initiation. Also, we will compare the cost of secondary distribution of HIVST in two populations, MSM and MLWH, to further complement studies exploring the cost-effectiveness of secondary distribution strategies in PLWH.

We will use innovative strategies based on the HIVST secondary distribution model to improve case-identifying management efficiency and target social networks of MLWH for accurate interventions with the help of the one-stop service platform. We aim to promote HIV testing in the social networks of MLWH, expand testing in high-risk populations, cut off high-risk HIV transmission pathways, and explore more effective secondary distribution models. This will provide an important theoretical basis for further promoting the application of these intervention technologies in other populations and other regions.

